### 6.3 MEASURES TO MINIMIZE BIAS: RANDOMIZATION AND BLINDING

#### **Randomization Plan**

Randomization will be stratified by site.

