## 9.2 SAMPLE SIZE DETERMINATION

We propose to randomize 474 patients to one of three surgical arms (158 per surgical arm). We will follow another 158 non-surgical patients meeting the inclusion/exclusion criteria. Sample size was determined to have adequate power for Aim 1 based on the primary outcome of the MHQ summary score at 12-month follow-up. **We expect to have complete data for 12-month follow-up time from 126 patients in each group, after accounting for a conservatively estimated 20% decrease in sample size from losses to follow-up.** For Aim 1, we expect 126 patients per group to give 80% power to detect an 8 point difference in the mean MHQ summary scores between VLPS and CRP and between VLPS and EFP using a mixed-effects model with a two-sided 0.025  $\alpha$ -level test. This assumes a standard deviation (SD) of 18 points (corresponding to an effect size of 0.44 SD), an average of 24 patients per site and an intra-site correlation coefficient (ICC) of 0.012. **To adjust for potential within surgeon correlation, we will also consider either a three level hierarchical model with surgeons nested within site, or use surgeons instead of sites as random intercepts. If technical variation is mostly between surgeons, addressing within surgeon correlation will reduce the ICC, which would give larger power to detect the same effect size. Covariate adjustments will likely give greater power by reducing the variability when the covariates are associated with the outcome and are not highly correlated with other covariates in the model.** We expect the 8 point difference in MHQ score at 12-months as a minimally detectable and meaningful difference between VLPS and either CRP or EFP. Our retrospective study of patients treated with VLPS showed mean ( $\pm$ SD) MHQ scores of 77 ( $\pm$ 15) at 3 months, 81 ( $\pm$ 17) at 6 months, and 85 ( $\pm$ 18) at 12 months for elderly patients. We believe the observed improvement of 8 points from 3 to 12 months to be similar to the expected post-surgical improvement difference between VLPS surgery compared with either EFP or CRP.

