For Aim 2, the proposed sample size and longitudinally assessed outcomes will provide 80% power to detect a between-group difference in the monthly rates of improvement of 0.22 points or greater with an  $\alpha$  level of 0.025, assuming a within-person correlation of 0.2 and ICC of 0.012. **For Aim 3, we consider power for a hypothetical scenario in which VLPS effect is smallest in the least active and largest in the most active patients. The study will have 83% power to detect the difference in the effect sizes for the VLPS to CRP group of 0.05 SD in the lowest, 0.30 SD in the moderate and 1.0 SD in the highest activity subgroups based on a 2 by 3 two-way analysis of variance, assuming about even number of patients in the three baseline activity subgroups. We note that though we do not hypothesize a differential effect of treatment in any subgroup, we will have adequate power to detect a differential treatment effect as large or larger than the hypothesized scenario, and the study will have adequate power to detect predictor effects that are homogeneous across subgroups as long as the predictor effects are as large as the effect size associated with the surgical procedures.** Aim 4 will compare outcomes between the combined surgical groups versus non-surgical group in which we expect the difference to be larger than the differences between VLPS and either EFP or CRP. We therefore expect the statistical power using the proposed number of non-surgical group patients to be more than adequate to make this comparison.

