As described in Section C11 under Aim 1, a small portion of patients may cross over intra-operatively from a randomly assigned procedure of EFP or CRP to VLPS. Whether the analysis is done using intent-to-treat or as-treated, such cross-over cases may result in somewhat smaller effect sizes than when there were no cross-over cases. Nonetheless, having outcomes measured longitudinally over a 24-month period gives the study adequate power to detect a time-averaged difference between two surgical arms much smaller than the difference based only at 12 months. Specifically, the proposed study gives 80% power to detect a time-averaged difference as small as 4.8 points, using a 0.025 level two-sided test based on mixed-effects model with three follow-up assessments and assuming an SD of 18 and a within-person correlation of 0.2. In addition, using the as-treated analysis, in a worst case scenario in which 10% of both EFP and CRP patients cross over to VLPS, sample size will not be equal across the three groups. This, however, will not affect the power significantly. Specifically, we will still have 80% power to detect a time-averaged difference in the MHQ scores of about 5 points between EFP or CRP (N = 113 per group) to VLPS (N = 152) with 0.025 level test. The power calculations were done using NQuery Advisor 7.0 (Saugus, MA), with appropriate considerations for longitudinally measured data.

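### Aim 2's claim of 80% power for a slope difference of 0.22 points per month does not follow from Section 9.2's own inputs, which give about 30 to 40%

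*Protocol*

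**What the plan says.** Protocol Section 9.2 gives three power statements.

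- **Aim 1, 12-month MHQ:** "126 patients per group to give 80% power to detect an 8 point difference" at a two-sided 0.025 level, with SD 18 and "an average of 24 patients per site and an intra-site correlation coefficient (ICC) of 0.012". The 126 comes from 158 randomised per arm less 20%: "We expect to have complete data for 12-month follow-up time from 126 patients in each group".
- **Aim 2, recovery trend:** "80% power to detect a between-group difference in the monthly rates of improvement of 0.22 points or greater", at an alpha "level of 0.025, assuming a within-person correlation of 0.2 and ICC of 0.012". The SD, the number per group, the visit times and the covariance form are not restated.
- **Time-averaged difference:** "80% power to detect a time-averaged difference as small as 4.8 points". The inputs given are SD 18, a correlation of 0.2 within patients and three assessments after surgery; the calculation is described as "using a 0.025 level two-sided test based on mixed-effects model".

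Three other places bear on Aim 2. The Schedule of Activities (Section 1.3) has the full MHQ at 6 weeks and at 3, 6, 12 and 24 months; enrolment and 2 weeks have only its pain domain. Section 9.4.2 plans a longitudinal mixed model that compares slopes, with an autoregressive covariance tried first. Section 6.3 says "Randomization will be stratified by site".

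**The concern.** A slope difference of 0.22 points per month is small beside the Aim 1 target. Over the 22.5 months from 6 weeks to 24 months it amounts to 0.22 × 22.5 = 5.0 MHQ points. With a within-person correlation of only 0.2, repeated visits remove little patient-level variance from a slope, so 126 per group looked too few.

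Recovery trend is a listed secondary objective with a directional hypothesis: slower recovery with EFP and CRP than with VLPS. If the stated power is wrong, a null slope comparison would be reported as having had an 80% chance of finding a 0.22-point difference when the real chance was about half that or less.

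**Working it through.** **Inputs.** n = 126 per group, SD 18 (variance 324), within-person correlation ρ = 0.2, two-sided alpha 0.025, all from Section 9.2. SD 18 and the two-sided test are carried over to Aim 2 as assumptions. Visit times are 1.5, 3, 6, 12 and 24 months (Section 1.3). Normal quantiles are 2.2414 (alpha) and 0.8416 (80% power), sum 3.083.

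**Step 1: the other two figures reproduce.**

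- Aim 1: design effect 1 + (24 − 1) × 0.012 = 1.276. SE = 18 × √(2 × 1.276/126) = 2.56. Power at 8 points = Φ(8/2.56 − 2.2414) = 81%; 80% is reached at 7.90 points.
- Time-averaged: variance per patient 324 × (1 + 2 × 0.2)/3 = 151.2. Detectable difference 3.083 × √(2 × 151.2/126) = 4.78, stated as 4.8. No site inflation is used.

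The second match supports n = 126, SD 18 and ρ = 0.2 as the section's working inputs.

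**Step 2: Aim 2.** For a slope difference between two groups with equal correlation between visits, SE = √(2 × SD² × (1 − ρ)/(n × Sxx)), where Sxx is the sum of squared deviations of the visit times.

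- Mean time = 46.5/5 = 9.3. Sxx = 60.84 + 39.69 + 10.89 + 7.29 + 216.09 = 334.8.
- SE = √(2 × 324 × 0.8/(126 × 334.8)) = 0.111.
- Power at 0.22 = Φ(0.22/0.1109 − 2.2414) = Φ(−0.26) = 40%.
- Difference detectable with 80% power = 3.083 × 0.1109 = 0.34 points per month, or 7.7 points over 22.5 months.

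**Step 3: vary the inputs.** Inflation multiplies the variance by 1.276. The autoregressive rows use the generalised least squares slope variance, with correlation 0.2 between adjacent visits and 0.2 to the power of the number of visits apart otherwise.

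| Change from Step 2 | SE | Power at 0.22 | 80% power at |
|---|---|---|---|
| None | 0.111 | 40% | 0.34 |
| Site inflation 1.276 | 0.125 | 31% | 0.39 |
| First-order autoregressive | 0.129 | 30% | 0.40 |
| Both of these | 0.146 | 23% | 0.45 |
| Six visits, adding 2 weeks (Sxx 399.3) | 0.101 | 47% | 0.31 |
| 158 per arm, no losses | 0.099 | 49% | 0.31 |
| SD 15 | 0.092 | 56% | 0.28 |
| Seven times, adding time 0 as well (Sxx 451.9) | 0.095 | 53% | 0.29 |
| Seven times and 158 per arm | 0.085 | 63% | 0.26 |

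A two-sided 0.05 test (the same as one-sided 0.025) gives 51% with five visits.

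**Step 4: what 0.22 would need.** With five visits and the other inputs unchanged, 80% power at 0.22 needs one of these:

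- 3.083² × 2 × 324 × 0.8/(334.8 × 0.22²) = 304 evaluable patients per arm
- a within-person correlation of about 0.67
- an SD of about 11.6

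**The case against.** **The inputs for Aim 2 are not fully stated.** This stands. The SD is not repeated, and the proposed sample size could mean 158. The 126 counts complete 12-month data, and a mixed model also uses earlier visits from patients lost later. A single figure of 40% would therefore claim too much precision. However, every case above that keeps SD 18 and alpha 0.025 stays at or below 63%. The stated 0.22 can be approached only by stacking departures: SD 15, all 158 per arm, no site inflation, and a full MHQ at time 0 and 2 weeks give 3.083 × √(2 × 225 × 0.8/(158 × 451.9)) = 0.219. That sets aside the SD and the losses used elsewhere in Section 9.2, and the visit schedule.

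**Aim 2 does not rest on one straight line.** Section 9.4.2 expects a plateau, allows several ways to model time and also compares groups at 24 months. This limits the damage, but the power statement is about a linear monthly rate and must be right on those terms.

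**Stronger readings that the documents do not support.**

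- A reader might infer that Aim 1's 80% is also wrong. It reproduces from its stated inputs. With randomisation stratified by site and site fitted as a random effect, the inflation is conservative: without it, SE = 18 × √(2/126) = 2.27 and power is about 90%. Conservative planning is not an error.
- A reader might infer that a factor of 2 was dropped, since 3.083 × √(324 × 0.8/(126 × 399.3)) = 0.221. That match needs a full MHQ at 2 weeks, which the schedule does not have, and other input sets also give 0.22. It is a possible source and cannot be shown.
- A reader might infer that the trial is too small. It was sized on Aim 1 alone.

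**Conclusion.** The Aim 2 power statement is wrong as written. On Section 9.2's inputs, with SD 18 carried over and the five full-MHQ visits, power at 0.22 points per month is about 40% under equal correlation without site inflation. It is about 30% with either the site inflation or an autoregressive covariance. The difference detectable with 80% power is about 0.34 to 0.40 points per month (0.45 if both are applied), roughly one and a half to two times the stated figure.

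The result rests on a linear slope, a normal approximation and the assumed SD. A smaller SD softens it (56% at SD 15) without rescuing it. The primary comparison and the sample size are unaffected.

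A minor point of presentation is that the section calls the time-averaged difference much smaller than the 12-month one. It sets 4.8, which carries no site inflation, against 8, which does. On one footing the pairs are 4.8 and 7.0 without inflation, or 5.4 and 7.9 with it. The time-averaged figure is smaller either way.

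**What to change.** In Section 9.2, restate Aim 2 as 80% power for a slope difference of about 0.34 to 0.40 points per month, or as about 30 to 40% power at 0.22. In the same sentence name the SD, the number per group, the visit times, the covariance form (matching the one Section 9.4.2 uses first) and whether site inflation is applied. If 0.22 came from other inputs, state them so that the figure can be reproduced.

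Optionally, note that the 8-point figure includes site inflation and the 4.8-point figure does not, and give both on one footing.

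The cost is a change of wording and one recalculation. No patients, visits or analyses change; one secondary power figure becomes less favourable.

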### 9.3 POPULATIONS FOR ANALYSES

The primary analytical approach will be intention-to-treat. An as-treated approach will be used for sensitivity analyses.

## 9.4 STATISTICAL ANALYSES

### 9.4.1 GENERAL APPROACH

The study design chosen is a Randomized Controlled Trial (RCT), because RCT's provide the most reliable form of scientific evidence. Few retrospective case control studies were conducted so far regarding distal radius fractures. A multicenter randomized clinical trial to define the optimal treatment for this prevalent injury in the elderly was not conducted so far.

### 9.4.2 ANALYSIS OF THE PRIMARY EFFICACY ENDPOINT(S)

**Aim 1:** *To compare 12-month post-surgical outcomes of elderly DRFs treated with VLPS with CRP and EFP.* Primary outcome will be the summary score of the MHQ. We will report means for each group and the mean difference between pairs of each group, along with their 95% confidence intervals. The primary outcome will be compared using a linear mixed-effects model to address the hierarchical nature of the data. The model will include surgeons nested within site and sites as random effects, fracture severity group indicator effect and two indicators for EFP and CRP groups. The surgical procedure indicators will each estimate the difference between EFP to VLPS and CRP to VLPS. We will also obtain covariate adjusted estimates of the between group differences; the covariates will be determined by the baseline analyses and will likely include age, baseline MHQ score, dominance of the injured hand and baseline RAPA score. Similar analyses will be done using other secondary outcome variables, including grip strength. We will also calculate MHQ score and grip strength as the difference (and %) of the uninjured hand scores. These measures may better reflect recovery because the uninjured hand can give a proxy measure of the patient-specific maximum achievable outcome. Analysis of complications will depend on how often they occur. For example, if the combined complications are rare, we will dichotomize them as present/absent and use a generalized linear mixed-effects model with logit link to compare the odds of complication between VLPS/EFP and between VLPS/CRP, while adjusting for within surgeon and site correlation. If the number of complications is substantial, we will use a count data model such as generalized linear model with log link to make the between-group comparison.

**Cross-over:** A surgeon may decide intra-operatively that the randomly assigned procedure is not amenable to the patient's particular fracture, which results in an intra-operative cross-over. Due to the nature of the surgery, such intra-operative cross-over cases will be limited to crossing from either of the two more conservative procedures (EFP or CRP) to VLPS, and we expect it to occur in < 5% of the cases. Intent-to-treat (ITT) will be the primary analytic method with participants retained in their randomized groups regardless of whether they have crossed over. The ITT estimates the use effectiveness and is the standard way to handle cross-over in randomized controlled trials and has been used in other DRF fixation studies. We will also do as-treated (AT) analyses in which groups will be defined by the procedure the patient ultimately receive. In this study, cross-over will likely give an under-estimate of the VLPS effect (compare with either EFP or CRP) with both ITT and AT analyses. This is because any cross-over will be to VLPS, the procedure expected to give better outcomes. With ITT analysis, the mean difference between VLPS and either EFP or CRP will likely be smaller because those who crossed to VLPS

(who would be expected to have better outcomes) will be analyzed as EFP or CRP. In surgical trials, another potential form of cross-over is a possible repeat surgery (of the same or different type) due to complication or failure to achieve acceptable reduction. In elderly DRF patients, most surgeons will not recommend another surgery due to less than desirable reduction. This is because there has been no evidence that failure to achieve reduction affects functional recovery. Even if a repeat surgery is desired, it will not be within a year from the initial surgery when functional problems occur.

**Missing Data:** We will describe the extent and pattern of missingness in outcome variables by the three groups. Although not expected to be more than 2-3%, we will assess the amount of missing data in baseline covariates as well. If missingness is less than 5% and missing data appear to be at random (e.g., depends on covariates, but not suspected to depend on unobserved outcome) or completely random, we will fit a model using complete data, adjusting for the covariates that missingness is found to depend on. On the other hand, if missingness is greater than 5%, we will impute the missing outcome values based on baseline prognostic factors, and 6-week and 3-month outcome values. Multiple imputation will be implemented using IVEware software, which was developed at the University of Michigan and uses a multivariate sequential regression approach. IVEware can impute all types of data (binary, categorical, count and continuous) and imputes missing values for each individual conditional on all observed values for that individual, and thus exploits correlational structure among covariates that include all other variables observed or imputed. We will then obtain parameter estimates of interest using the described analytic approach in which we will combine the estimates from the five imputed datasets, accounting for both within and between imputation variability.

**Aim 2:** *To compare the recovery trend for elderly DRFs treated with VLPS with CRP and EFP.* This aim is to provide an understanding of the recovery pace and long-term outcomes after DRF and subsequent treatment. We think patients will show steady improvement and will eventually reach a plateau in their outcomes, but we currently do not know how long it takes to reach the plateau and if significant differences in improvement occur in early months. We will first graphically explore the outcomes data over time by plotting cross-sectional means at each measurement time by surgical group and by plotting longitudinal outcomes over time for each individual to assess individual trends. We will use a longitudinal data mixed-effects model to assess and compare outcome trends over time within and across the three groups. The model will estimate the time-averaged outcomes for the three groups, the average slope over time in the VLPS group and the effect of EFP and CRP on the slope of the VLPS group. The EFP effect and the CRP effect on the average slope of the VLPS group is each hypothesized to be negative because we hypothesize the recovery rate of each to be slower than that of VLPS. We will use an autoregressive covariance specification first, but appropriateness of other covariance specification will also be considered. The graphical exploration will help us consider more complicated parameter structures of the mixed-effects models describing the trajectory of recovery, especially how the time and the correlation within patients will be modeled. This analysis will allow us to assess when the outcome differences occur and whether the differences remain over time using various ways to model time. In addition to comparing the rates of improvement over time, we will compare the outcome differences at 24 months. Similar analyses will be done using other secondary outcome

variables, such as grip strength and pain. As with Aim 1, we will model trends using the intention-to-treat and as-treated method.

---

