| Active Wrist Arc of Motion                                                                                                                                                                   | 86% $\pm$ 12%                 | 81% $\pm$ 10%  | 89% $\pm$ 12%                 | 84% $\pm$ 17%  | 92% $\pm$ 11%                  | 95% $\pm$ 17%  |
| Grip Strength                                                                                                                                                                                | 66% $\pm$ 19%                 | 44% $\pm$ 28%  | 78% $\pm$ 22%                 | 67% $\pm$ 35%  | 80% $\pm$ 22%                  | 77% $\pm$ 31%  |
| MHQ                                                                                                                                                                                          | 77 $\pm$ 16                   | 77 $\pm$ 15    | 83 $\pm$ 17                   | 81 $\pm$ 17    | 82 $\pm$ 18                    | 85 $\pm$ 18    |
| The MHQ is based on a scale of 0 to 100. The higher the scores, the better the subject's hand performance. Arc of Motion and Grip Strength are measured as a percentage of uninjured opposite hand. |                               |                |                               |                |                                |                |

[figure not shown]

We will extend our experience from these prior studies to perform a multicenter clinical trial to compare this new intervention to established techniques (EFP and CRP) in the elderly. Although the VLPS technique is a promising treatment, its outcomes, complication rate and cost have not been studied in a larger cohort of subjects in a clinical trial design. This study will be the first of its kind to define the most optimal treatment for elderly DRFs.

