### 10.1.6 DATA HANDLING AND RECORD KEEPING

#### 10.1.6.1 DATA COLLECTION AND MANAGEMENT RESPONSIBILITIES

#### 10.1.6.2 DATA COLLECTION FORMS

From each participant, data forms such as, Participant Demographic Questionnaire, RAPA, SF-36, MHQ, Hand Function Data form will be collected by the study coordinator at every visit. The surgeon will complete the Surgery Data form after surgery and complication checklist at every visit after surgery and these forms will also be collected by study coordinator.

The investigators will make every effort to preserve the study subjects' confidentiality. No one other than study personnel will have access to the study participants' records. Precautions will be taken to ensure that the records are in a locked cabinet. Records will not have the subjects' names listed on them, but instead an identification number will be assign to each subject, which only the investigators and study coordinators will be able to link to subject names. The subjects will also not be identified in any reports of this study.

To ensure compliance with the protocol, the Coordinating Center will create a MOP that is identical for each site. The MOP will be finalized after the study planning period. The MOP will contain instructions on how to complete all aspects of the study including randomization, measurements, data entry, and a copy of all study forms.

Data collection forms:

- Adverse Event Reporting form – Consists of the AE's with details pertaining to date of event, type of event, related or not, action taken and event outcome.
- Comorbidity Checklist – Questionnaire filled out by the participant at enrollment about their existing medical illness.
- Distal Radius Fracture Complication Checklist and Score Sheet- Form filled out by surgeon (PI) after surgery and every follow up visit, has information on complications developed such as nerve or bone/joint or tendon complications after surgery.
- General Health Questionnaire- information on general health in between follow up visits.
- Hand Edema Form – Measure of fingertip to palmar crease distance.
- Hand Function and Range of Motion data sheet- Measures grip, pinch and wrist range of motion of the injured arm and the normal arm.
- Hand Therapy Data Sheet – Information on type of therapy completed, number of visits, and when therapy was terminated.
- Inclusion/Exclusion Criteria – Includes fracture type and the detailed criteria for eligibility.

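### For grip strength, subtracting the uninjured hand is never more precise than adjusting for it; the uninjured-hand value should enter the model as a covariate

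*Protocol*

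**What the plan says.** Section 9.4.2 (Aim 1) sets a linear mixed model for the MHQ summary score, with covariate-adjusted estimates alongside. The covariates are to come from the baseline analyses and "will likely include age, baseline MHQ score, dominance of the injured hand and baseline RAPA score". Secondary outcomes, grip strength among them, are to be analysed in the same way. The section then continues: "We will also calculate MHQ score and grip strength as the difference (and %) of the uninjured hand scores". The reason given is cautious: "These measures may better reflect recovery because the uninjured hand can give a proxy measure of the patient-specific maximum achievable outcome".

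Both hands are measured. Section 10.1.6.2 says of the hand function form: "Measures grip, pinch and wrist range of motion of the injured arm and the normal arm". The Schedule of Activities (Section 1.3) places that form at follow-up visits from 6 weeks on, and the visit list in Section 8.1.4 also has it at 2 weeks. Neither has it at enrollment.

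Table 1 in Section 2.2 reports the investigators' earlier results on the percent scale: "Arc of Motion and Grip Strength are measured as a percentage of uninjured opposite hand". Elderly grip there is 44% (SD 28%), 67% (SD 35%) and 77% (SD 31%) at 3, 6 and 12 months.

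**The concern.** The uninjured hand is useful because it carries information on how strong a patient's grip would be without the fracture. Using it should remove between-patient variation from the comparisons of VLPS with EFP and with CRP. The protocol uses it in only two fixed ways. Subtraction assumes that each extra unit of grip in the good hand goes with exactly one extra unit in the injured hand. Where the true slope is below 1, subtraction over-corrects and carries part of the good hand's own variation into the outcome. A regression adjustment estimates the slope instead.

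The covariate rule does not clearly supply this. Candidate covariates come from baseline analyses (Sections 9.4.2 and 9.4.5), and the uninjured hand is not measured at baseline. Grip therefore ends up with an unscaled, a difference and a percent version, and the version that uses the good hand by estimating its slope is missing. What is at stake is precision on a secondary outcome.

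**Working it through.** **The protocol's own figure.** It states no precision or power for grip. The only related figure is the MHQ sample size in Section 9.2 (8 points, SD 18, two-sided 0.025, 80% power, 24 per site, ICC 0.012). It reproduces: 2 × 18² × (2.2414 + 0.8416)² / 8² = 96.2; design effect 1 + 23 × 0.012 = 1.276; 96.2 × 1.276 = 122.8, so 123 against the stated 126. The comparisons below borrow only the 126 per arm and the 0.025 level.

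**Difference against adjustment.** Let the injured-hand SD be 1, the uninjured-hand SD be k, and the correlation r.
- Difference score variance: 1 + k² − 2rk
- Adjusted variance: 1 − r²
- Excess of the difference: (k − r)², which is never negative and is zero only when r = k, that is, when the slope r/k is 1.

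At k = 1 the ratio adjusted/difference is (1 − r²)/(2 − 2r) = (1 + r)/2:

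| r (assumed) | Difference | Adjusted | Ratio |
|---|---|---|---|
| 0.3 | 1.40 | 0.91 | 0.65 |
| 0.5 | 1.00 | 0.75 | 0.75 |
| 0.7 | 0.60 | 0.51 | 0.85 |
| 0.9 | 0.20 | 0.19 | 0.95 |

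A ratio of 0.75 means that the difference score needs 1/0.75 = 1.33 times the patients for the same precision. With unequal SDs at r = 0.5, the two variances are 0.84 and 0.75 for k = 0.8, and 1.31 and 0.75 for k = 1.25.

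The difference is less precise than the unscaled injured-hand value when r < k/2. That threshold is 0.5 at equal SDs, but 0.417 if the SDs are 0.25 (uninjured) and 0.30 (injured).

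**Percent against adjustment.** This was simulated with 4,000 trials per setting, 126 per arm, critical value 2.2414 and no clustering. The assumed effect is 0.10: of mean uninjured grip in the additive setting, and in the ratio itself in the proportional setting.

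Additive relation, both hands with SD 0.3 of mean uninjured grip:

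| r | Unscaled | Difference | Percent | Adjusted |
|---|---|---|---|---|
| 0.3 | 65% | 50% | 44% | 70% |
| 0.5 | 66% | 65% | 63% | 79% |
| 0.7 | 67% | 88% | 87% | 93% |

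Proportional relation, ratio mean 0.77 and SD 0.31 as in Table 1:

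| Uninjured-hand CV | Difference | Percent | Adjusted |
|---|---|---|---|
| 0.2 | 61% | 63% | 61% |
| 0.3 | 59% | 64% | 60% |
| 0.4 | 53% | 62% | 55% |

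Percent leads adjustment by about 2, 4 and 7 points here. Adjustment still matches or beats the difference.

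**How good a maximum is the uninjured hand?** From Table 1, elderly grip, under normality:
- 12 months: (100 − 77)/31 = 0.74, upper tail 22.9%
- 6 months: (100 − 67)/35 = 0.94, upper tail 17.3%
- 3 months: (100 − 44)/28 = 2.00, upper tail 2.3%

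At 12 months a gamma distribution gives 20.9% and a lognormal 19.3%. The mean and SD alone do not settle it. An SD of up to √(77 × 23) = 42.1 is possible with every value between 0 and 100%, so 0% above is possible. The upper bound is 31²/(31² + 23²) = 64.5%.

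**The case against.** The difference and percent are additions. An unscaled grip analysis is already planned, with dominance of the injured hand a likely covariate, so most of the proposed model exists and one covariate is new. The percent scale is also the one on which the investigators reported grip before, and it describes relative recovery, which is a different question from an absolute difference. All of this stands. It is why percent should be kept and why the point is minor.

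A reader might go further and infer that the protocol's own data refute its rationale, with over a fifth of grip values above the maximum. The documents do not support that. Table 1 gives means and SDs and no count above 100%; the fifth is an inference for 12 months under an assumed distribution. The protocol says only that "the uninjured hand can give a proxy measure of the patient-specific maximum achievable outcome", and a proxy can be exceeded. The same normal calculation would put 20% of 12-month MHQ scores above 100, although "The MHQ is based on a scale of 0 to 100"; a grip ratio has no such ceiling, but the example shows the limits of the method.

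Nor do the documents show that adjustment beats percent in general, since the result turns on whether the hands relate additively or proportionally. The MHQ version cannot be judged in the same way, because the protocol reports no uninjured-hand MHQ data.

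The remaining objection is that the covariate is measured after randomisation. That is true, and adjustment then assumes that treatment does not affect the good hand. The planned difference and percent use the same value and need the same assumption. Nor is this merely detail for a SAP, which is not at hand: the protocol itself fixes subtraction as one of its forms.

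**Conclusion.** The point holds for the grip difference score. Linear adjustment is never less precise than subtraction, and the two are equal only when the slope is 1. At equal SDs the adjusted variance is 65% to 85% of the difference score's for r from 0.3 to 0.7. These values of r are assumptions, and the protocol gives neither a between-hand correlation nor an uninjured-hand SD. At r = 0.9 the gain shrinks to 5%.

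Against percent the ranking depends on the model. About a fifth of 12-month elderly grip values would exceed the uninjured hand if they are roughly normal, so calling that hand a proxy for the maximum is weak rather than wrong. The primary MHQ comparison and the sample size are not touched.

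**What to change.** In Section 9.4.2, for grip strength, replace the difference score by the injured-hand value as outcome in the mixed model already described, with the uninjured-hand value from the same visit and dominance of the injured hand as covariates. Name this as the comparative grip analysis. Keep percent of the uninjured hand as a supportive measure, and state that all forms using that hand assume it is unaffected by treatment.

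The cost is about one sentence. No new data are needed, since the hand function form records both hands. What is given up is a few points of power relative to percent if the two hands are in fact proportional; the retained percent measure would still show that result.
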